*Boussé district, Burkina Faso.* Boussé is a rural area situated 40 kilometers northwest of the capital Ouagadougou. The entomological inoculation rate (EIR) is less (around 200 infectious bites per year). Most transmission occurs between July and October. At least 90% of children aged 6 – 59 months carry malaria parasites during this period. It is estimated that each child under five years of age experiences about 0.8 clinical attacks of malaria per year. ITN coverage is currently low.

*In Mali, the trial will take place in the following health centres: Djoliba, Siby and Ouelessebougou in Kati administrative region. Djoliba is located in a rural setting 60km southwest of Bamako with a population of 30000 inhabitants. Siby is located 45 km west of Bamako and the health centre covers a population of 15,232 inhabitants. Ouelessebougou is situated 80 km south of Bamako and provides service to 34,600 inhabitants*. The rainy season extends from June to October with an annual rainfall of 800 – 1200 mm. Malaria transmission is seasonal. The EIR is in the range of 100-150 infectious bites per person per season. Children have about 2 clinical attacks of malaria per year and the prevalence of parasitaemia at the end of the transmission season is about 70%. ITN usage is low.

Characteristics of the two study sites are summarized in Table 1.

**Table 1**. Characteristics of the study sites.

Variable Site

Bousse Doliba, Siby and Ouelessebougou **

Demographic 74,000 -

surveillance

Transmission June- Nov July-Nov

season

Rainfall [contact]

mm/year

Net coverage in

children < 5 years

Untreated < 3% <3%

Treated < 1% <7%

Clinical attacks per 0.8 2

year in children < 5 years

Parasite prevalence 85-95% 40 - 75%

in children < 5 years

First-line treatment AL AS/AQ or AL

of malaria***

** Because of an impending malaria vaccine trial it may be necessary to move the IPTc

study to an adjacent community.

*** AQ = amodiaquine; AS = artesunate; AL = artmether/lumefantrine (Co-Artem)

*Recruitment and randomization*

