The incidence of clinical malaria in unprotected children aged 3 – 59 months living in the study area detected by passive surveillance is likely to be in the range of 1.0 -2.0 clinical attacks per year and the incidence in those sleeping under an ITN will be about one half of this (0.5 to 1.0 clinical attacks per year). Assuming that children experience an average of 0.5 attacks per year of sufficient severity to present to a health facility, and the need to detect a 20% reduction in this incidence (ie. from 0.5 to 0.4 attacks per year) in children who receive IPT, the smallest reduction that would be likely to make IPT a worthwhile investment, and allowing for a 20% loss to follow-up, approximately 2,000 children (1,000 in each arm) will be required at each site to give a study with 90% power and 95% precision. A study of this size will have greater than 90% power to detect a 20% reduction in the estimated prevalence of parasitemia from 50% to 40% at the end of the rainy season. The study will have a slightly lower power to detect a 20% increase in the incidence of malaria or the prevalence of parasitemia during the second period of observation due to some loss to follow-up (likely to be in the range of 10 – 20 %). Pooling of data across sites will increase the power of the study to detect a small rebound effect.

It is estimated that the rate of hospital admissions with malaria will be in the range of 20 to 60 per 1,000. Assuming a median incidence rate of 40 per 1,000, approximately 120 admissions with severe malaria might be anticipated in children in the control arm of the study. The study will, therefore, have at least 90% power to detect a 50% reduction in admission with severe malaria (from 40 to 20 per 1,000). Initially, estimation of the impact of IPTc on admission with severe malaria was to be assessed using pooled data from three sites (MRTC, CNRFP and Navrongo Health Research Centre) and that the trial in Navrongo was suspended in June 2008 (due problems in getting ethical clearance), the number of children (2,000) who were to be enrolled at the Navrongo site has now been split between CNRFP and MRTC. Therefore the number of children to be enrolled in each of the two sites has been increased to 3,000 (1500 per arm). The study will not be powered to detect an effect on mortality but deaths will be recorded and investigated for safety reasons.

*Insecticide treated nets*

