Immediately after recruitment to the trial, the mother or guardian of each study child will be provided with a long lasting, insecticide treated net (LLIN) that is marked with an identification number. Instructions will be given to the parent or guardian on how to use the net and the importance of using the net on the bed/sleeping place of the study child will be emphasized. If a child already has a net, this will be replaced and the old net returned to the family for their use. Utilisation of LLINs by study children will be monitored during home visits made to collect blood films (see below) and during the cross-sectional survey conducted at the end of the malaria transmission season.

*Intermittent preventive treatment*

Study children will be treated with a course of SP + AQ or matching placebos on three occasions during the malaria transmission season. Drugs will be pre-packaged to facilitate administration. Monthly doses will be timed to cover the peak transmission season at each site, July/August/September in Burkina Faso and Aug/Sept/Oct in Mali. Doses of AQ and SP will be based on weight as shown in Table 2. AQ will administered on the base of 10 mg/kg daily for 3 days and SP will administered as a single dose of 25mg/kg of sulphadoxine + 1.25 mg of pyrimethamine. Full tablets containing the exact daily dose (AQ) or the dose for a full course (SP) will be manufactured to avoid having to split tablets which may lead to administration of inadequate doses.

**Table 2**. Dosage of study drugs.

Weight groups Amodiaquine* SP**

Tablets (Daily dose) tablets (single dose) **

Sulfadoxine Pyrimethamine

5-9 kg 70 mg 175 mg 8.75 mg

10-18 kg 140 mg 350 mg 17.5 mg

19 kg+ 220 mg 550 mg 26.25 mg

Note. * Tablet given for 3 days;  ** tablet given for 1 day

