Drugs will be given under observation at a central point in the village. Children will be asked to stay at the distribution point for 30 minutes after drug administration. If vomiting occurs during this period, drugs will be re-administered. If vomiting recurs this will be noted but the drugs will not be given on a third occasion. Such children will not be excluded from the trial and they will be eligible to receive drugs at the subsequent monthly treatment. If a child misses the day set for treatment, a home visit will be made to enquire why the child was not brought for treatment and this will be recorded. If the family would like the child to continue with treatment but he or she was unable to attend on the specified day, then the first dose of treatment will be reoffered within 3 days and treatment must be completed within a maximum of 7 days after the designated date for each round. A dose missed on second of third day of treatment must be administered with 48 hours of the planned date. Thus, no child will receive two doses of SP + AQ at an interval of less than three weeks.

*Safety of IPT with SP and AQ*

Safety of SP and AQ will be monitored in all children on days 0, 1 and 2 of treatment administration and on day 3 (day after the last dose of treatment for each treatment round). .At the second and third treatment rounds, the families of each study child will be asked whether the child has had any symptoms that might have been drug related since the previous drug administration round.

Serious adverse events, including deaths and hospital admissions, will be recorded throughout the 18 months of surveillance. The likely relationship of the adverse event to drug administration will be determined according to standard criteria. Serious adverse effects will be reported to the Data Safety and Monitoring Board (DSMB) within a period specified by the board.

*Surveillance for malaria*

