Surveillance for clinical attacks of malaria will start at the time of the first administration of study drugs (July/August 2007) and continue until the end of the second malaria transmission season (November 2008). Clinical episodes of malaria will be detected using a system of augmented passive surveillance. In each study area, project staff will be posted to the health centers in the area (3-5) where children in the trial are likely to go for treatment if they develop malaria. All children who attend one of these centers will be screened to determine whether or not they have been enrolled in the trial. Children identified through their identity card and/or health card as being study subjects will have their temperature recorded. A finger prick blood sample will be obtained from all study children with fever (an axillary temperature of 37.5 0 C or higher) or a history of fever within the previous 24 hrs for preparation of a blood film, measurement of hemoglobin (Hb) concentration and for a rapid diagnostic test (RDT) for malaria. Those who have a positive RDT for malaria will be treated immediately for malaria according to national guidelines (AS + AQ or AL). Children with anemia will be treated according to the national protocol.

Project staff will identify any study child admitted to hospital with a possible diagnosis of malaria and ensure that their investigation includes examination of a blood film and determination of Hb concentration. The clinical features of these children will be documented on a standardized questionnaire and their clinical course followed.

To obtain more information on the impact of IPT on the prevalence of malaria infection over time in the study population, at each site a random sample of 150 children will be visited at home once a week during the peak period of malaria transmission during the first and second years of the trial. During the intervening dry season, 300 children will be visited once every four weeks. The temperature of each child will be taken and a blood film obtained regardless of whether or not a child has fever. A rapid diagnostic test will be done on any child who has fever (axillary temperature of 37.5 0 C or higher) or a history of fever within the previous 24 hrs and if this is positive treatment will be given according to national guidelines (AS+AQ or AL).

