The revised version of the protocol specifies that children who miss the first dose of IPTc administration of a given treatment round must be visited within 3 days of the planned date of visits instead of 7 days as mentioned in the previous version of the protocol. The three doses of each IPTc course must be completed within 7 days of starting the first dose of IPTc In addition, children who miss the second or the third dose of each IPTc course must be seen within 48 hours. The reason for this approach is to make sure that the interval between IPTc courses is at least 21 days.

1. Surveillance of malaria morbidity

The previous version of protocol indicates that filter paper samples will be taken from sick children to assess markers of resistance to SP and AQ. The steering committee has decided not to take filter paper samples from sick children because the value of these samples to understand the effect of IPTc on drug resistance markers is questionable. Furthermore the study doses not have adequate resources to collect these samples and to analyse them.

1. End of malaria transmission season cross-sectional survey

The previous version of the protocol indicates that weight and height were the anthropometric parameters to be measured during the survey. However after discussion with an anthropologist it was suggested to measure child’s arm circumference during this survey. Now the protocol is amended that mid arm circumference will also be measured during child’s screening for enrolment in the trial to provide baseline information.

1. Slide reading

The previous version of the protocol stated that 100 high power field were to be examined before a slide is declared negative. According to the revised protocol all fields in a slide must be examined before a blood smear is declared negative for malaria parasites

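### In Mali the plan allows AS + AQ treatment during an SP + AQ round, so a few active-arm children could take amodiaquine from both on the same day; naming AL around each round prevents this

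*Combined protocol and SAP*

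**What the plan says.** **Treatment of cases.** Section IV.1, Surveillance for malaria, covers study children seen at health centers with fever or a recent history of it: "Those who have a positive RDT for malaria will be treated immediately for malaria according to national guidelines (AS + AQ or AL". The same two options apply to children found febrile and RDT-positive at home visits. No exception is made for days on which study drug is given.

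**Which site.** The first-line row of Table 1 reads "First-line treatment AL AS/AQ or AL": AL for Boussé, AS/AQ or AL for Mali. The table footnote gives AQ as amodiaquine and AL as artemether/lumefantrine.

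**Study drug.** In Intermittent preventive treatment: "AQ will administered on the base of 10 mg/kg daily for 3 days". There are three monthly rounds, in August, September and October in Mali.

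**Timing rules.** A missed first dose is re-offered within 3 days, and a round must be complete within 7 days of its designated date. For later doses: "A dose missed on second of third day of treatment must be administered with 48 hours of the planned date". The amendment section explains: "The reason for this approach is to make sure that the interval between IPTc courses is at least 21 days".

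**Acute malaria at entry.** Recruitment and randomization does not exclude such children. They are treated, randomized and kept in the trial.

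**Safety.** "Safety of SP and AQ will be monitored in all children on days 0, 1 and 2 of treatment administration", and again on day 3. Section V adds reporting to the DSMB and a local safety monitor at each site.

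**The concern.** Two instructions meet in one child and neither mentions the other. A Mali child who becomes ill around a round is treated at once, possibly with AS + AQ, and is also due amodiaquine or placebo on three days. The timing rules set latest dates for study doses, and their stated purpose is the gap between study courses. They do not address amodiaquine given as treatment.

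If AS + AQ starts on day +1 or +2, the round is under way and the 48-hour limit leaves little or no room to separate the doses. If it starts on days −2 to 0, the limits would let staff space the doses, but nothing tells them to.

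At stake is additional amodiaquine on top of an IPT course in children under five, in the active arm only. Monitoring on days 0 to 3 would record a reaction but would not prevent the exposure.

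**Working it through.** The plan states no figure on this point, so there is none to reproduce. The check is a text comparison (above) and a rough count.

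**Inputs**
- Active arm in Mali: 1,500 (Sample size).
- Presenting attacks per child-year: 0.5 (Sample size). A higher value of 1.0 follows from "Children have about 2 clinical attacks of malaria per year" in Mali, halved by nets: "the incidence in those sleeping under an ITN will be about one half of this (0.5 to 1.0 clinical attacks per year".
- IPT efficacy e: 20%, the smallest worthwhile reduction (Sample size), to 95%, reported for SP + AQ in Senegal (Executive Summary, Background and Rationale).
- Assumed: all attacks fall evenly over 152 days (Mali's July to November season in Table 1 is 153 calendar days), AS + AQ lasts three days, and every attack is treated with it.

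**Daily rate.** 0.5/152 = 0.00329; 1.0/152 = 0.00658.

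**Overlap window per round, w**
- w = 2 days if staff space doses whenever they can, so that only starts on days +1 and +2 overlap. A three-day course starting on day −2, −1 or 0 ends on day 0, 1 or 2. The first study dose can then fall on day 1, 2 or 3 (within the 3-day re-offer) and the last on day 3, 4 or 5 (within 7 days).
- w = 5 days (starts on days −2 to +2) if doses are not spaced.

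**Children affected over three rounds**
- Efficacy applies in every round: 1,500 × [1 − exp(−rate × w × 3(1 − e))].
- No protection yet in round 1: 1,500 × [1 − exp(−rate × w × (1 + 2(1 − e)))].

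| Attacks/year | w | e | Efficacy in all rounds | None in round 1 |
|---|---|---|---|---|
| 0.5 | 2 | 95% | 1.5 | 10.8 |
| 0.5 | 2 | 20% | 23.5 | 25.4 |
| 0.5 | 5 | 95% | 3.7 | 26.9 |
| 0.5 | 5 | 20% | 58.1 | 62.8 |
| 1.0 | 2 | 95% | 3.0 | 21.6 |
| 1.0 | 2 | 20% | 46.6 | 50.4 |
| 1.0 | 5 | 95% | 7.4 | 53.3 |
| 1.0 | 5 | 20% | 113.9 | 123.0 |

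The range is about 1.5 to 63 children at 0.5 attacks per year (0.1% to 4.2%) and about 3 to 123 at 1.0 (0.2% to 8.2%). The low end depends heavily on whether efficacy applies in round 1; the high end hardly does. All counts halve if AS + AQ and AL are used equally, and are zero if only AL is used.

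Two features push the counts up. Rounds sit in peak transmission, so an even spread understates attacks near them. Treatment also needs only fever, or a history of it, and a positive RDT, in a population with 40–75% parasite prevalence (Table 1).

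**Daily dose.** The study dose is nominally 10 mg/kg. The documents give no AS + AQ dose. If it carries 10 mg/kg of amodiaquine, the shared-day total is about 20 mg/kg; if 7.5 to 15, it is 17.5 to 25.

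**Burkina Faso.** No overlap is expected, because Table 1 lists AL only.

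**The case against.** **Harm is not shown.** This stands. A reader might infer that the plan exposes children to a toxic dose. The documents do not support that: the AS + AQ dose is absent, nothing describes the effect of doubled amodiaquine, and the Challenges section calls SP + AQ side effects minor. The 10 mg/kg figure sets the IPT dose; it is not a ceiling on amodiaquine from all sources.

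**Same-day overlap is an arbitrary line.** This stands in part. Spacing the doses can move AS + AQ to days 0–2 and IPT to days 3–5. At an assumed 10 mg/kg from each, that is six consecutive days and the same 60 mg/kg in total. Re-offering the round is therefore not a remedy, and the fix below does not use it.

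**Staff could already avoid it.** Project staff identify study children by card, AL is permitted in Mali, and they need only know that a round is under way, not the child's arm. Standard operating procedures, mentioned in the Budget Narrative, may cover the point. All true, but the protocol does not require it, and monitoring acts after the exposure.

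**Restricting treatment to AL has a scientific cost.** This stands. Resistance markers to amodiaquine are a secondary endpoint in both arms. AL throughout the season would remove therapeutic amodiaquine from the Mali placebo arm and change that contrast. It would also be broader than the problem, which is confined to the days around a round.

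**Conclusion.** The gap is real and small. Following the plan as written, some active-arm children in Mali could take amodiaquine from treatment and from IPT on the same day, and nothing in the available text prevents it. The counts in the table are illustrative. They rest on AS + AQ always being chosen, three-day courses and an even spread of attacks, none of which the documents establish.

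A reader might also infer that the efficacy result is compromised. It is not: an attack is counted on fever and parasite density, whatever drug is then chosen, so the primary endpoint is unaffected. This is a cheap safety improvement at one site, not a flaw in the design.

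**What to change.** **Surveillance for malaria:** state that study children in either arm in Mali who need malaria treatment, from 2 days before a round's designated date until that round's 7-day completion limit, receive AL.

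**Intermittent preventive treatment:** state that if AS + AQ is nevertheless given in that window, the remaining amodiaquine or matching placebo doses of that round are omitted in either arm and recorded as missed. The child stays in follow-up and is analysed as randomized. This fallback cannot undo a dose already taken that day, so AL comes first. Applying both rules to both arms protects the blind.

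**Cost:** two sentences and some AL. The window is 10 days (−2 to +7), or 30 days over three rounds. For all 3,000 Mali children with no efficacy assumed, 3,000 × 0.5/152 × 30 = 296 courses, and 592 at 1.0 attacks per year. These are upper figures under the even-spread assumption, and some of those courses would be AL anyway. Prices are not in the documents. If AL runs out, a few amodiaquine or placebo doses are omitted. Therapeutic amodiaquine use falls slightly, which should be noted when the amodiaquine resistance-marker endpoint is interpreted.

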After village meetings have been held in each study area to explain the nature of the trial, a census of children under five years of age resident in the study area will be conducted. At each site, approximately 3,100children aged 3 – 59 months will be selected randomly from the census list for initial screening. The families of these children will be visited by a member of the field team and invited to participate in the study. If a family agrees that a child can join the trial, signed, informed consent will be obtained from a parent or guardian in the presence of an independent witness. Children will then be screened for their eligibility to join the trial until 3,000 have been entered. Screening will include administration of a questionnaire which asks about previous illnesses, clinical examination and measurement of height and weight.

Inclusion criteria will be –

- Age 3 – 59 months.
- Permanent residence in the study area with no intention of leaving during the surveillance period.
- Provision of informed consent.

Exclusion criteria will be -

- Temporary residence in the study area.
- Absence of informed consent.
- Presence of a severe, chronic illness such as severe malnutrition or AIDS, likely to interfere with evaluation of the trial results.
- A history of a previous, significant adverse reaction to either of the study drugs.

An acute illness, such as malaria, will not be an exclusion criterion. Such illnesses will be treated appropriately, the child randomized and retained in the trial. Children who are invited to join the trial but who are excluded for one of the reasons indicated above will be given an ITN but will not be followed further.

Children will be individually randomized using a standard computer program which gives randomization within blocks of varying number. Separate randomization lists will be generated for each site. In order to reduce the chances of the investigators becoming aware of the drug code during the course of the trial, for example because of an increased incidence of vomiting in one group, ten randomization groups will be used, five for active drugs and five for placebo. Children enrolled in the trial will be issued with a photo identity card and the parents or guardian will be asked to present this whenever their child is taken to a health centre or hospital to ensure that the child is seen by a member of the study team.

*Sample size*

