At the end of the malaria transmission season, a cross sectional survey will be undertaken at which each child will be examined, their height, arm circumference and weight recorded and a finger prick blood sample obtained for determination of Hb concentration, preparation of blood films and collection of a filter paper sample for subsequent studies on the prevalence of molecular markers of resistance.

Any death in a study child will be investigated within a month of death using the post-mortem questionnaire technique.

*Surveillance for ‘rebound’ malaria*

Passive surveillance for malaria will be continued during the dry season and the subsequent malaria transmission season to determine if IPT impairs the development of natural immunity to malaria, reflected in an increase in the incidence of malaria in children who have received IPT during the previous year (rebound malaria). Identical surveillance techniques to those described above, including a final cross-sectional survey, will be used during the second year of observation.

*Surveillance for drug resistance*

Molecular markers associated with resistance to amodiaquine and to SP will be investigated in children with malaria parasitemia before and after the peak malaria transmission season to determine whether resistant parasites are selected by IPT. At baseline (before treatment administration) children will be sampled from a census database list for the prevalence of markers of resistance to SP and AQ. These children will have a clinical examination, a thick and thin blood film and filter paper blood spot prepared, and haemoglobin concentration will be determined. Samples will be collected as set out in Table 3.

**Table 3.** Samples for testing for molecular markers at each site.

Study group Number of samples Number likely to be Number for

collected positive for malaria molecular assays

Year 1

Random sample 750 300 150**

children < 5 years

before intervention *

Cross-sectional

survey – post intervention

IPT 1500 300 150**

Placebo 1500 750 150**

Year 2

Cross-sectional

survey

IPT 1500 750 150**

Placebo 1500 750 150**

Notes.

* These children will not be included in the trial but will come from the same area.

** Random sample from the positive blood samples available.

Thus, during the first year of the study approximately 450 samples will be tested from each site and during the second year 300 giving a total of 1,500 over the two years of the trial.

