*Severe malaria*. Severe malaria will be defined according to the WHO criteria [Trans R Soc Trop Med Hyg 2000;94 suppl 1]. Joint training of staff from each site will be undertaken to ensure standardization in the recording of symptoms and signs that are used to make a diagnosis of severe malaria before the trial commences.

*Anemia*. Anemia will be defined as an Hb concentration <11 g/dl, moderate anemia as an Hb concentration < 8 g/dL and severe anemia as an Hb concentration < 5 g/dl.

*End-points*

The primary end-point for the first and second years of the study will be the incidence of clinical malaria, detected by passive case detection, defined as above.

Secondary endpoints will be –

(a) the incidence of clinical malaria using a definition that does not require a parasite

density threshold,

(b) the incidence of severe malaria as defined above,

(c) the incidence of anemia among children seen at a hospital or health centre,

(d) the prevalence of parasitemia at the end of malaria transmission season cross-

sectional survey,

(e) the prevalence of anemia at the end of malaria transmission season cross-sectional

survey,

(f) the prevalence of stunting and the proportion of children underweight at the end of

malaria transmission season cross-sectional survey,

1. the proportion of children with parasites carrying resistance markers to amodiaquine, SP

or sulfonamides at the end of transmission season cross-sectional survey,

1. the incidence of all cause hospital admissions,

(i) the incidence of hospital admissions due to malaria,

(j) the number of malaria treatments received by each child.

*Data management and analysis*

As far as possible, identical forms, in English or French, will be used at each site. Data will be double entered at each site and validated. An individual analytical plan will be prepared for each site together with an analysis plan for the combined data from the three sites. These plans will be submitted for approval by the DSMB established for the trial before the code is broken. Breaking the code and initial analysis of the trial results will be done at a meeting of the investigators.

*Ethics*

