**Protocol amendments**

**Date 20th June 2008**

**Amendments to version 1 of the protocol (20th June 2008)**

**Summary of changes made**

The trial steering committee comprising staff from the London school of Hygiene and Tropical medicine and the trial Principal investigators at the sites in Africa met in March and June 2008 and made the following amendments to the protocol the version of the protocol as described below. These amendments will be submitted to Ethics committee of institutions participating in the trial.

1. Dosage of sulfadoxine-pyrimethamine and amodiaquine

It was indicated in the protocol that sulphadoxine-pyrimethamine (SP) and amodiaquine (AQ) dosage will be based on child’s age. Four age categories were constituted. However, considering the difficulty of correctly estimating child’s age in rural communities, the study steering committee agreed that drug administration based on child’s weight will be more appropriate in routine programme settings. Therefore three weight groups have been constituted (5-9 kg; 10-18 kg and 19 kg and over). The exact daily dose (AQ: 70mg for 5-9kg, 140 mg for 10=18kg and 220 mg for 19+kg; SP: 175 mg + 8.75 mg for 5-9 kg; 350 mg +17.5 mg for 10-18 kg and 550 mg + 26.75 mg for 19+kg) will be manufacturing for each weight to avoid breaking tablets in halves or quarters, which may results in inadequate dosage of drugs.

1. Trial sites

Ethical clearance was obtained for the conduct of the study in Burkina Faso and Mali. The third trial site (Navrongo Health Research Centre) was not successful in getting ethical clearance from the Ghana Food and Drug Board (FDB). The FDB raised some queries which the site is currently addressing. However, it is feared that obtaining ethical clearance after re-submission of a revised protocol to the FDB is likely to take at least 2 months which will cause a significant delay in the implementation of the study. Therefore it was agreed to suspend the trial in Navrongo. Consequently, sections relating to the Navrongo Health Research Centre have been removed from the protocol.

1. Randomization

The first version of the protocol indicates that randomisation will be done in 8 blocks (4 blocks per group). To minimise risk of “unblinding” of research staff, the number of blocks was increased to 5. Thus, randomization will now be done in permuted blocks of 10 (5 blocks per group).

1. Samples size

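### Growth, endpoint (f), is specified only as end-of-season stunting and underweight prevalence, with no planned use of the height and weight measured at screening; baseline-adjusted z-scores would be more precise at almost no cost

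*Combined protocol and SAP*

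**What the plan says.** Section IV, End-points, lists ten secondary endpoints. The only one on growth is (f): "the prevalence of stunting and the proportion of children underweight at the end of" the season, taken at the cross-sectional survey.

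Paired measurements will exist. Under Recruitment and randomization, screening includes "clinical examination and measurement of height and weight". Under Surveillance for malaria, at the end-of-season survey "each child will be examined, their height, arm circumference and weight recorded". Under Surveillance for 'rebound' malaria, the same techniques, "including a final cross-sectional survey, will be used during the second year of observation", so a third measurement follows about a year later. The amendment summary also adds arm circumference at screening, for "enrolment in the trial to provide baseline information".

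No section defines a z-score, a change from baseline or a baseline-adjusted growth comparison. The Definitions section gives haemoglobin cut-offs for anaemia but none for stunting or underweight. Statistical methods are deferred for all endpoints: "An individual analytical plan will be prepared for each site together with an analysis plan for the combined data from the three sites" (the count of three predates the move to two sites). The plans go to the DSMB for approval before unblinding.

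**The concern.** The treatment rounds and year-1 surveillance fall between July and November, so the first survey comes only a few months after enrolment. In children aged 3–59 months, whether a child is below a height-for-age cut-off at that point depends heavily on how tall the child was at entry. That between-child variation is noise for the treatment comparison, and the child's own baseline can remove much of it. Reducing a continuous measurement to a yes/no status loses further information.

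Age error adds to the noise. The amendment summary changed the dosing basis "considering the difficulty of correctly estimating child’s age in rural communities". The remark concerns dosing, but height-for-age and weight-for-age depend on the same recorded ages. If one birth date or age basis is used at both visits, much of its error is shared by the two z-scores and is absorbed by adjustment; a single reading against a cut-off has no such protection. The documents do not allow this part to be quantified.

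What is at stake is sensitivity. A modest growth benefit could pass unnoticed in the prevalences, and a wide interval around zero could be read as absence of effect.

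**Working it through.** **Inputs from the protocol (Sample size).** 1,500 per arm per site; 20% loss to follow-up; 90% power; the stated 95% precision is read as two-sided alpha 0.05. Hence 1,500 × 0.8 = 1,200 per arm at one site and 2,400 pooled. The multiplier is 1.960 + 1.2816 = 3.2415.

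**Inputs assumed.** Prevalence p = 30% (range 10–50%); correlation r between baseline and survey z-score of 0.5, 0.7 or 0.9; a 0.10 SD shift to illustrate power.

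**The plan's own figure.** No power is stated for growth. The nearest figure is over 90% power for parasitaemia prevalence of 50% against 40% with 1,000 per arm. Recomputed: 99.5% with 1,000 per arm and 98.1% with 800. The plan's figure holds.

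**Smallest detectable difference, prevalence.** 3.2415 × √(2p(1−p)/n).
- One site: 3.2415 × √(2 × 0.3 × 0.7/1,200) = 0.0606, about 6.1 points. Dividing by the normal density at the 30% cut (0.3477) gives 0.174 SD, a first-order conversion.
- Pooled: 3.2415 × √(0.42/2,400) = 0.0429, about 4.3 points, or 0.123 SD.

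**Smallest detectable difference, mean z-score adjusted for baseline.** 3.2415 × √(2(1−r²)/n), in SD units.

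| r | One site (1,200) | Pooled (2,400) |
|---|---|---|
| 0 (unadjusted) | 0.132 | 0.094 |
| 0.5 | 0.115 | 0.081 |
| 0.7 | 0.095 | 0.067 |
| 0.9 | 0.058 | 0.041 |

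**Power for a 0.10 SD shift (30.0% against 26.6%).**

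| Analysis | One site | Pooled |
|---|---|---|
| Prevalence, unadjusted | 45% | 74% |
| Prevalence, adjusted for baseline z-score, r = 0.5 / 0.7 / 0.9 (simulated) | 52 / 56 / 81% | not run |
| Mean z-score, unadjusted | 69% | 93% |
| Mean z-score, adjusted, r = 0.5 / 0.7 / 0.9 | 81 / 93 / >99% | 98 / >99 / >99% |

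The simulated row uses 500 trials per setting, so it carries a standard error of about 2 points. At 20% or 40% prevalence, the unadjusted prevalence comparison has 39% or 48% power at one site and 66% or 78% pooled.

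**Information retained by the unadjusted prevalence.** Dichotomising alone keeps φ²/[p(1−p)], where φ is the normal density at the cut: 34%, 49%, 58%, 62% and 64% at p = 10, 20, 30, 40 and 50%. Relative to the adjusted z-score, multiply by (1−r²). Across p = 10–50% this leaves 26–48% at r = 0.5, 18–33% at r = 0.7 and 7–12% at r = 0.9. At the most favourable prevalence, half is lost once r² exceeds 1 − 0.5/0.637 = 0.215, that is, r above about 0.46.

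**The case against.** The strongest reply is that an endpoint list is not an analysis plan. The protocol gives no analysis method for any endpoint, the plans are still to come, and a prevalence model adjusted for baseline would be fully consistent with (f). Adding arm circumference at screening as baseline information suggests that the investigators value baseline anthropometry. A reader might infer that the baseline will be discarded; the documents do not say so, and silence does not show it. What remains is that plans written to the endpoint as worded would analyse a binary outcome, and adjusting that outcome recovers only part of the loss (52–81% power against 81% to over 99%).

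A reader might also infer that a growth benefit would be undetectable. It would not: a 0.10 SD shift has 45% power at one site and 74% pooled. Nor do the documents predict any growth effect, so a null result cannot be forecast.

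The claim that most of the information is lost, or that the adjusted analysis is worth several times as many children, depends on a prevalence and a correlation that the protocol does not give. Dichotomising alone loses more than half only at prevalences of about 20% or less.

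The year-2 survey also counts against an overstatement. (f) is not restricted to year 1, and a year after enrolment the baseline explains less of current size, so the gain there may be smaller.

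Finally, the argument does not extend to anaemia in (e), because haemoglobin is not among the listed screening measurements.

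Prevalence is unbiased under randomisation and is the natural measure for a policy audience. That stands, and it is a reason to keep it.

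**Conclusion.** The point holds as one of precision. (f) is the only growth endpoint, it is binary, and no use of the screening height and weight in its analysis is specified. Under an assumed 30% prevalence, the planned comparison detects about 0.17 SD at one site and 0.12 SD pooled. Baseline-adjusted z-scores detect about 0.115 to 0.058 SD and 0.081 to 0.041 SD respectively, for assumed correlations of 0.5 to 0.9. The adjusted z-score is the more efficient analysis at every prevalence and correlation examined; how much more cannot be settled from the documents. The endpoint is secondary and no bias is involved, so neither the trial's primary conclusion nor the validity of the prevalence comparison is affected.

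**What to change.** In the analysis plans to be approved before the code is broken:

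- Pre-specify for (f) a comparison of mean height-for-age and weight-for-age z-scores at the survey, by linear model adjusted for the child's baseline z-score and age, and for site when pooled.
- Use the same recorded birth date or age basis for each child at both visits.
- Apply the same analysis at the year-2 survey.
- Keep stunting and underweight prevalence as reported outcomes, adjusted for baseline status, and state the cut-offs that define them.

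The cost is plan wording only, since every measurement is already scheduled. The small drawback is that a z-score difference is less directly interpretable for policy than a prevalence, which is why the prevalences stay in the report. Specifying this now avoids a change of scale after unblinding that would look post hoc.
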